#### Exposure

To assess participants’ exposure to the program, group facilitators took attendance on-site, using a list of participants. They then transcribed this information when they received their brief post-session questionnaire, online.

#### Differentiation

While some participants in the experimental condition may have not fully engaged in the program, some parents in the wait-list condition might have gained access to some of the program’s content. Indeed, contamination was possible since we decided to randomly assign participants within each participating school. This procedure was chosen over a cluster randomized trial to avoid conflating our experimental manipulation with schools’ characteristics, such as their size, socio-economic status (SES), educational philosophy, and to remove this unexplained between-school variability from the between-group main effect, thereby increasing statistical power.

Because all parents in the study heard about the program during the information meeting (see Recruitment section below), some parents assigned to the wait-list condition may have decided to buy and read the book (and try some skills). However they could not take part in the program, which presumably fosters increased learning due to group participation (e.g., weekly sessions with facilitators and other parents, exercises, homework, discussion and modeling). To control for this potential confound, we asked parents in the wait-list condition whether they had bought and read the book. Finally, to ensure differentiation between the How-to Parenting Program and other interventions as well as between the experimental and the control conditions, parents in both conditions were asked to document any intervention and/or a therapeutic activity used for their family.

### Outcomes

Most parenting program studies emphasize E problems since they are disruptive, but I problems are also an important source of suffering and need to be prevented. Moreover, assessing the level of children’s strengths and well-being allows for a complete account of their mental health. The primary outcome measure is children’s I and E mental health problems, as assessed by their parents. Secondary outcome measures include other indicators of children’s mental health, as teachers rated children’s E and I problems and socio-emotional strengths and children rated their subjective well-being. Secondary outcomes also include the three dimensions of optimal parenting (as perceived by children, in addition to parental reports) and parents’ own mental health (indicators of both symptoms and well-being).

### Participant timeline

All parents and children completed their questionnaires before randomization (pre-intervention; T1), 1 week after the seven-week program (post-intervention; T2), and again at 6-month (T3) and 1-year (T4) follow-ups to assess change over time (see Table 2). Teachers each completed two questionnaires, since children’s teachers at the beginning of the study (T1 and T2, in February and April) were not the same teachers as during the last part of the study (T3 and T4, in October and April of the following school year).

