#### Secondary hypotheses

We also expected that children of parents assigned to experimental groups would experience decreases in teacher-rated E and I problems as well as increases in teacher-rated strengths and in child-reported well-being over time, whereas children whose parents were on the wait-list would not show such improvements during that year (i.e., stable or increasing psychological problems; stable or decreasing strengths and well-being).

We also expected that parents assigned to experimental groups would show improvements in parenting over time (i.e., increases in parental affiliation, structure and AS), whereas parents in control groups would not show such improvements (i.e., stable or declining parenting quality) during that year. Lastly, parents assigned to experimental groups were expected to experience improvements in their own mental health (decreases in symptoms and increases in well-being) compared to parents in control groups who would not show such improvements over time (i.e., stable or declining parental mental health). Based on parenting and motivation research, we also expected that increases in parental affiliation, structure and AS would mediate the expected improvements in children’s mental health.

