#### Teachers

The research coordinator met with participating schools’ teachers during one of their scheduled meetings, to briefly provide them with key information about the study. Teachers learned about the overall procedure and about what their possible participation would entail, i.e., filling-out a questionnaire about one or more of their pupils, on two occasions (either at T1 and T2, or at T3 and T4). Since children move to the next grade the following year, new teachers were also contacted and asked to fill-out the third (T3) and last (T4) TRs. All teachers for whom parental consent were obtained received their own consent form and paper-pencil questionnaires, in their school mailbox.

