### Statistical methods

We will adopt an intent-to-treat approach [68] as this approach increases external and internal validity. Our data will also be hierarchical in nature; pre-intervention, post-intervention, 6-month and 1-year follow up measures will indeed be nested within each parent, who are nested within a parenting group. Accordingly, multivariate hierarchical linear modeling (HLM) analyses will be conducted to test our hypotheses; these analyses have the advantages of estimating error terms while taking into account the nested nature of the data and allow for missing data without decreasing power. Analyses will thus include all participants who completed at least one assessment, regardless of the number of sessions they attended (for the experimental groups).

To evaluate change over time, the four assessment points (pre-intervention, post-intervention, 6-month follow-up, and 1-year follow-up) will be treated as repeated measures to estimate change between each subsequent time points [69]. This approach is chosen because it allows rates of change to differ across time.

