#### Primary analyses

The effect of the How-to Parenting Program will be evidenced by significant interactions between rates of change and experimental conditions. These interactions should reveal that child mental health increases over time for participants in the experimental condition, but not for participants in the control condition. Based on our pilot study, we expect that the program will be effective to decrease parent-reported I and E problems.

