### Strengths

In addition to assessing an intervention that taps the three key aspects of optimal parenting, the present study has other important strengths. The study uses multiple informants, along with a large sample size and longitudinal follow-ups, even though for teacher-reports, respondents will have changed within the year-long study. Rigorous methodological procedures also include the distinction made between the implementation and the evaluation team members in order to limit social desirability, the blindness of teachers and RAs, and the fidelity assessments. Other ethical and methodological strengths include the non-stigmatizing invitation to all parents, the absence of exclusion criteria based on parents’ or children’s difficulties and the practical choice of local schools for the study’s setting, instead of clinics. Choosing to recruit and offer the program in local schools also helped to make this intervention non-stigmatizing. In a related vein, given that this study was designed as a universal rather than a selected preventive intervention, parents who had more than one child in grade school could not decide which child would be evaluated. This procedure avoided potential sampling biases, such as having a higher proportion of higher-risk children in the sample.

Importantly, the study has high ecological validity, as it was offered by a heterogeneous group of facilitators, with some who, apart from receiving a 3-day training, had no extensive background in program implementation and/or optimal parenting. Since this minimal training was an exposure to the program’s content, former participating parents could easily become facilitators, a relatively simple and low-cost way to foster sustainable dissemination. Together, the relatively low cost of the manualized material, the minimal training required (compared to extensive training and/or expensive certifications) and the possibility of offering the program within schools greatly increase the potential outreach of this program, thereby facilitating accessibility of parenting resources to interested parents. In general, though the present study is not a cost-effectiveness project, the large effect-sizes reported in our pilot study conducted with a population-based sample supports that it may be worth using this program as a universal approach to preventing child psychological problems and improve child mental health by fostering optimal parenting.

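### Teacher-rated outcomes change rater between T2 and T3, so within-arm change over that interval cannot be read as improvement or stability, and the planned successive-change contrasts lose precision

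*Protocol article*

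**What the plan says.** The Participant timeline states that the teachers who rate at T1 and T2 (February and April) "were not the same teachers as during the last part of the study", that is, at T3 and T4 in October and April of the next school year. The Teachers section agrees: each teacher completes a questionnaire "on two occasions (either at T1 and T2, or at T3 and T4").

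Under Statistical methods, the four assessments "will be treated as repeated measures to estimate change between each subsequent time points". No exception is made for teacher reports, and the nesting described is time within parent within parenting group.

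Under Primary analyses, a program effect "will be evidenced by significant interactions between rates of change and experimental conditions", and those interactions are expected to show improvement in the experimental condition but not in the control condition. Secondary analyses names no other criterion. Secondary hypotheses expects, in the experimental arm, "decreases in teacher-rated E and I problems as well as increases in teacher-rated strengths", against stable or worsening scores on the wait-list.

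The Strengths section concedes that "for teacher-reports, respondents will have changed within the year-long study". No analysis section says what follows from that.

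**The concern.** Of the three successive intervals, T2–T3 is the one in which the person giving the score changes. A rise or fall within an arm from April to October can come from the new teacher's use of the scale as well as from the child. The hypotheses are worded as within-arm patterns (a fall in one arm, no improvement in the other), so the teacher hypothesis could look supported or refuted because of the new rater alone.

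The second issue is precision. A benefit at 6 months or 1 year, measured against baseline, must be built from contrasts that cross the switch. The T1–T2 interval covers only about two months, and a benefit that is simply maintained after T3 gives no arm difference in T3–T4 change.

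The Participants section gives two reasons for collecting teacher reports: to test generalization to school and to obtain reports from blind respondents. Parents, who supply the primary outcome, know their allocation. A teacher analysis that is imprecise or misread at follow-up weakens both purposes.

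**Working it through.** **Inputs from the article.** The planned size reproduces: 4 waves × 8 groups = 32 groups; 4 × 64 = 256 parents; 256 × 4 = 1024 time points. Four schools per year over 4 waves give 16 schools, and 256 / 16 = 16 families per school. Equal allocation gives 128 per arm. Families are randomized within school, and teachers are asked not to find out allocation. The article gives no TCRS variance, between-teacher correlation or number of teachers per school. All such values below are assumptions, on a scale where each rating has SD 1.

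**Step 1: what the T2–T3 change contains.** Within an arm, the expected change is the child's change plus the mean rater shift. Between arms, the shift has the same expectation on both sides and cancels. A simulation checked this: 4,000 trials per setting, 16 schools × 16 families, 1:1 within school, 6 teachers per school, child variance share 0.5, rater share 0.2, and a new random teacher at T3. Values are in SD; negative means fewer problems.

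| Rater shift | True effect | Change, program arm | Change, wait-list | Difference | Rejection rate |
|---|---|---|---|---|---|
| 0 | 0 | 0.00 | 0.00 | 0.00 | 4.6% |
| +0.3 | 0 | +0.30 | +0.30 | 0.00 | 4.4% |
| +0.3 | −0.3 | 0.00 | +0.30 | −0.30 | 66.6% |
| −0.3 | 0 | −0.30 | −0.30 | 0.00 | 4.2% |
| −0.3 | −0.3 | −0.60 | −0.30 | −0.30 | 68.1% |

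In row 3 a real improvement appears as no change in the program arm. In row 4 both arms appear to improve with no effect at all. The between-arm difference is right in every row.

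**Step 2: what the switch costs.** Let the child share be 0.5, the rater share s, and the occasion share e = 0.5 − s. The change has variance 2e with one teacher and 2e + 2s = 1.00 with two. Power is for 128 per arm and a 0.3 SD difference.

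| s | SD, same teacher | SD, new teacher | Power, same | Power, new |
|---|---|---|---|---|
| 0.1 | √0.8 = 0.89 | 1.00 | 77% | 67% |
| 0.2 | √0.6 = 0.77 | 1.00 | 87% | 67% |
| 0.3 | √0.4 = 0.63 | 1.00 | 97% | 67% |

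For a 0.5 SD difference, power with a new teacher is still 98%.

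**Step 3: what adjustment recovers.** Let r be the correlation between T1 and a later rating by a different teacher. The change from T1 has variance 2(1 − r). The later rating adjusted for T1 has variance 1 − r². The ratio is (1 + r)/2. Both estimate the same between-arm effect at T3 or T4, because randomization makes the expected T1 means equal.

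| r (assumed) | 2(1 − r) | 1 − r² | Variance ratio | SE ratio | SE reduction |
|---|---|---|---|---|---|
| 0.2 | 1.60 | 0.96 | 0.60 | 0.775 | 22.5% |
| 0.3 | 1.40 | 0.91 | 0.65 | 0.806 | 19.4% |
| 0.4 | 1.20 | 0.84 | 0.70 | 0.837 | 16.3% |

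Since 2(1 − r) exceeds 1 whenever r is below 0.5, differencing across teachers is then noisier than ignoring the T1 rating. Step 2 implies a cross-teacher correlation of 0.5, so the two illustrations rest on different assumptions and should not be combined.

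**The case against.** The strongest reply is that the test named in the plan is a between-arm interaction, and within-school randomization removes the rater shift from it. This stands. A reader might infer that the teacher-rated T2–T3 contrast is nothing but a rater switch, or that teacher ratings cannot show a program effect. The documents do not support either. The contrast is unbiased between arms, and T1–T2, which contains the program, and T3–T4 each have a single teacher. Bias would need teacher change, or teachers' awareness of allocation, to differ by arm, and nothing in the article says that it does.

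It can also be said that (1 + r)/2 is the general advantage of adjustment over change scores and does not measure the rater switch. That is fair. The switch matters because it lowers r: at an assumed same-teacher r of 0.7 the ratio is 0.85 and the standard error gain only 8%.

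These outcomes are secondary, and the respondent change is disclosed. Power holds up at the 0.5 SD that Sample size expects, although the pilot behind that figure had no teacher reports.

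Finally, rater terms for one instrument could be left to a fuller analysis plan. That would answer a complaint about missing detail. Here the article does fix the contrasts and the wording of the hypothesis, and both fit poorly with its own data collection.

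**Conclusion.** The point holds as a matter of interpretation and precision, not of bias. Within-arm teacher-rated change from T2 to T3, and any within-arm change from T1 to T3 or T4, cannot support a claim of decrease or stability. The between-arm contrast is valid but noisier than it need be: with cross-teacher correlations of 0.2 to 0.4, adjusting for T1 cuts the standard error of the T3 or T4 effect by about 16 to 23% relative to a change from T1. That range is assumed, and the power figures are illustrative for the same reason. They also take all 256 families as having teacher reports, which separate parental and teacher consent makes unlikely. A reader might infer that the trial's main result is at risk; it is not, since the primary outcome is parent-rated. The change is worth making because it is inexpensive and protects the only outcomes rated by respondents whom the article describes as blind.

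**What to change.** For the TCRS outcomes only:

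- Estimate the between-arm difference at T2, T3 and T4, adjusted for the T1 rating, within the mixed model. Enter all four waves as outcomes, constrain the T1 mean to be equal across arms, and leave the within-child covariance unstructured so that same-teacher and cross-teacher correlations can differ. Unlike an ordinary T1 covariate, this keeps children without a T1 teacher rating, in line with the plan to include everyone with at least one assessment.
- Repeat the analysis without T1 teacher reports collected after the first session, since the equal-mean constraint relies on T1 preceding the program. The Data collection methods section already codes these reports.
- State that within-arm T2–T3 teacher change will not be interpreted.
- Reword the teacher part of Secondary hypotheses as lower problems and higher strengths than wait-list at T2, T3 and T4.

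The cost is a separate model specification for the teacher outcomes and one reworded hypothesis. No new data are needed.

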**Table 2 Tab2:**
[figure not shown]
Schedule of Enrolment, Intervention and Assessments of the How-to Parenting Program RCT

### Sample size

The pilot study suggests that medium effects can be expected (i.e., Cohen’s d around.5) [48] and the primary focus of the present study pertains to cross-level interactions. Hox [49] suggests that these effects depend more strongly on the number of groups than on the total sample size. Tabachnick and Fidell [50] further suggest that sufficient power for cross-level effects is obtained when the number of groups is 20 or larger, whereas Paterson & Goldstein [51] recommend having at least 25 groups. Following these recommendations, our goal was to have 32 level-3 units (parenting groups), 256 level-2 units (parents), and 1024 level-1 units (time points). Sufficient power was expected since this number of parenting groups is above the recommended threshold and allows for recruitment drawbacks.

### Recruitment

The goal was to conduct the study within four grade schools per year, for 4 waves (recruiting about 64 parents to form 8 groups at each wave; see Flowchart in Fig. 1). The RCT began after obtaining ethics approval and funding. We first sought approval from three school boards, a prerequisite for soliciting school principals. We then sent information to school principals by mail at the beginning of each wave (September), who could contact the research coordinator for further information if they were interested in this program implementation and evaluation. There was no inclusion or exclusion criterion for school recruitment; all schools were invited. Given that we did not target specific types of schools nor SES neighborhoods, school participation first depended on school principals’ interest. When a school principal was interested in our study, information was given to all families by sending an information flyer via children’s schoolbag, in December. Parents then communicated their interest in the program by returning the flyer’s response section (reply slip). We asked teachers to refrain from recommending the parenting program to certain parents, to highlight its universal and voluntary nature. Recruitment thus also depended on each particular school’s general level of parental interest since the next recruitment stage (information meeting) could take place solely in schools in which a large number of parents returned their reply slip.

**Fig. 1 Fig1:**
[figure not shown]
Flow of participants for the How-to Parenting Program RCT, planned over four waves

If both parents of a same family expressed their wish to take part in the parenting program, we allowed them to do so (when there was enough space in a group) although data from the second, “duplicate” parent would not be used in statistical analyses. Identifying which parent was the participating one was decided by randomly choosing one of their sealed envelopes. Whether one or two parents participated in the program was coded, to examine whether this factor influences the program’s efficacy.

### Consent and allocation

Information meetings for parents were held in schools in January. One of the principal investigators met with interested parents to provide them with information about the parenting program and its assessment. Parents were thus informed about the How-to Parenting Program, the random assignment, their voluntary participation as well as that of their participating child and his/her teachers. Parental consent forms were filled out at the end of that information meeting. This consent form comprises three distinct sections, allowing parents to give their consent (or not) separately for (a) their child’s participation, (b) their child’s teachers’ participation and (c) their own.

Random assignment of families was made after parents’ T1 questionnaires were collected, within each school. The research coordinator extensively shuffled the sealed anonymous envelopes containing T1 questionnaires before randomly assigning them in one of the two conditions. Next, parents received a phone call informing them of the group they were assigned to (either in the group beginning the following spring or in the group beginning during spring of the following school year; see Fig. 1 and Table 2).

#### Blinding

Since parents knew in which condition they were assigned, their children may also have been aware of it. However, all research assistants (RAs) collecting child reports were blind to the intervention conditions, according to PROBE methodology to reduce assessment bias. Moreover, all teachers were asked to refrain from trying to know if a given pupil’s parent was taking part in the parenting program.

### Data collection methods

#### Parents

At the end of each information meeting, parents who had decided to take part in the study filled out a T1 paper-pencil questionnaire on site (see Instruments section below), after completing their consent form. When filling-out their T1 questionnaire, parents indicated whether they preferred to receive paper-pencil or online questionnaire. We thus either sent a paper-pencil version of T2, T3 and T4 by mail or provided parents a link, via email.

We collected all parent-reports (PR) at T1, prior to randomization. We also aimed to collect all of the T1 child-reports (CR) and T1 teacher-reports (TR) before the first session of experimental groups. We coded whether any of the CR or TR were collected after that, to verify whether including them influences the obtained results.

#### Teachers

The research coordinator met with participating schools’ teachers during one of their scheduled meetings, to briefly provide them with key information about the study. Teachers learned about the overall procedure and about what their possible participation would entail, i.e., filling-out a questionnaire about one or more of their pupils, on two occasions (either at T1 and T2, or at T3 and T4). Since children move to the next grade the following year, new teachers were also contacted and asked to fill-out the third (T3) and last (T4) TRs. All teachers for whom parental consent were obtained received their own consent form and paper-pencil questionnaires, in their school mailbox.

